## A non-significant trend for increased episodes of atrial fibrillation in patients treated with T3 has been shown in ThyRepair. Here, it should be noted that the use of inotropes such as epinephrine and dobutamine has been recently found to increase the odds of atrial fibrillation by 3.88 and 3.95 in pateints with septic shock.

## The increased temperature that was observed in some patients in ThyRepair study involved a single fever wave up to 38.5 during the second day of treatment that receded after paracetamol administration. This wave was recorded in 1 to 3 patients receiving T3. It didn’t cause any diagnostic issues since other inflammatory indices did not increase.

Thyroid hormones are eliminated 70-80% by the kidneys. In ThyRepair study we enrolled patients with GFR more than 60 ml/min and no problem was recorded after T3 administration. A reduction of GFR<30ml/min could increase T3 levels in blood. However, this increase is blunted by attenuation of the conversion of T4 to T3 which is reported under conditions of acute or chronic renal failure (37). It should be noted that the therapeutic index of T3 is high. In case there is a potential adverse event that could be linked to T3 in a patient with severe renal failure, urgent unblinding of the patient can be performed and the levels of T3 can be determined.

The liver has a secondary role in the elimination of thyroid hormones by 25%. Acute or chronic hepatic injury reduces the conversion of T4 to T3. Thus, in patients with hepatic injury, normal or increased levels of T4 and low levels of T3 have been reported. (Kano T, et al.. Serum thyroid hormone levels in patients with fulminant hepatitis: usefulness of rT3 and the rT3/T3 ratio as prognostic indices (38). Based on the above, administration of T3 in patients with hepatic injury will not result in higher than expected levels of T3 in blood.

Further analysis of preliminary data from ThyRepair show that although infarct size was similar between the placebo and T3 group, an improvement of LV ejection fraction is evident in T3 treated STEMI patients early and late after the index event (Figure 12 and 13).

***Figure 12.*** *CMR analysis shows no difference in infarct size (extent of injury) between placebo and T3 group.*

[figure not shown]

***Figure 13.*** *Left ventricular ejection fraction assessed by echocardiography at different time points in STEMI patients treated with placebo and T3.*

In a preliminary study (48), in 11 patients with severe septic shock that were all treated with dopamine, T3 was administered by continuous intravenous infusion in doses of 100-200μg/24h. In all patients, there was an increase in arterial blood pressure and dopamine dependence was terminated. T3 levels rose during infusion up to concentrations of 4 ng/ml and in some cases patients were treated up to 28 days without presentation of significant adverse events(48).

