**5.4 Measurement of thyroid hormone levels**

Serum total T3, total T4 and TSH will be determined by standard immunoassays at different timepoints: baseline and at 24h, 48h, 72h, and every 3 days till termination of drug administration or end of follow-up. All samples for thyroid hormone measurements will be collected and analyzed at the end in order not to break the blindness of the trial. The coefficients of variation for each assay will be less than 5 percent. The cost of thyroid hormone measurements will be covered by the sponsor.

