## The initial dose for the first 48hours is a high dose of T3 (therapeutic dose) exactly the same with the dose used in ThyRepair trial. Data show that this dose is safe (see below). Administration of T3 beyond 48 hours was not necessary in ThyRepair trial since these patients maintain T3 levels within normal range due to stable hemodynamic status and absence of other stress factors. In ThySupport trial, after the first 48hours, administration of T3 will continue with a maintenance dose which will be reduced by 50%. This is necessary because prolonged mechanical respiratory support and sepsis in these patients inhibit conversion of T4 to T3 and result in sustained reduction in T3 levels.

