## Thus, in ThySupport, the dose administered will be 0.8μg/kg i.v. bolus, starting within 60min after respiratory support and will be followed by an infusion of 0.113μg/kg/h i.v. for 48 hours (therapeutic dose). After the first 48h, a maintenance dose will be administered corresponding to 50% of the therapeutic dose (0.057 μg/kg/h i.v.). Drug administration will stop after successful weaning or end of followup (maximum 30 days).

***Figure 8.*** *Schematic of drug administration schedule inThySupport study*

In previous studies in CABG patients it was shown that administration of the dose of T3 proposed here (0.8μg/kg at the end of ischaemia followed by an infusion of 0.113μg/kg/h) resulted in short-term supranormal serum T3 levels without any effects on heart rate or arrhythmias or any other adverse event reported.

[figure not shown]

***Figure 9.*** *Pharmacokinetics of T3 in CABG patients*

More importantly, data from the ThyRepair study (EudraCT: 2016-000631-40) conducted in patients with ST-elevation myocardial infarction showed that administration of the drug under investigation at the proposed doses (0.8μg/kg i.v. bolus followed by an infusion of 0.113μg/kg/h i.v. for 48 hours) resulted in significant increase in the levels of T3 above normal that lasted for 72 hours without any significant adverse event.

[figure not shown]

***Figure 10****: Levels of triiodothyronine in serum during hospitalization in patients after acute myocardial infarction treated with placebo and T3*

Administration of high dose T3 resulted in a non-significant increase in heart rate during the first 3 days (Figure 11).

***Figure 11****: Heart rate assessed during hospitalization in STEMI patients treated with placebo and T3*

***Table.*** *Adverse events during hospitalization in Thy-Repair trial (interim analysis).*

| **Adverse Events** | **placebo Group**  **(n=17)** | **T3 Group**  **(n=16)** |  |
| --- | --- | --- | --- |
| Atrial Fibrillation | 7.7% | 19% | *p=0.25* |
| Thrombus in Left Ventricle | 12% | 12.5% | *p=0.94* |
| Pericardial Effusion | 6% | 6.25% | *p=0.9* |
| Minor Hemorrhages | 12% | 19% | *p=0.57* |
| Diuretics Use during first 24 hours | 40% | 50% | *p=0.7* |
| Need for Sympathomimetics administration after PPCI | 30% | 19% | *p=0.45* |
| Transient Fever wave>37.8 | 0% | 31% | *p=0.01* |

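### The protocol discounts T3 accumulation in renal and hepatic failure with an argument that does not cover infused T3, and T3 levels can be seen before the end only reactively

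*Protocol*

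**What the plan says.** **Renal and hepatic rationale (section 9, Dosage and Safety).** The protocol states "Thyroid hormones are eliminated 70-80% by the kidneys" and "A reduction of GFR<30ml/min could increase T3 levels in blood". It then offsets this: "However, this increase is blunted by attenuation of the conversion of T4 to T3". It adds that the therapeutic index is high, without a figure. For the liver, it argues from reduced conversion to the conclusion that T3 levels will not exceed expectation in hepatic injury.

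**Reason for the long infusion (same section).** Maintenance T3 is justified because "prolonged mechanical respiratory support and sepsis in these patients inhibit conversion of T4 to T3". The schedule is: "After the first 48h, a maintenance dose will be administered corresponding to 50% of the therapeutic dose". Treatment may last 30 days.

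**Safety data relied on.** "In ThyRepair study we enrolled patients with GFR more than 60 ml/min", and "Administration of T3 beyond 48 hours was not necessary in ThyRepair trial". The section also cites a preliminary study of 11 patients with septic shock given 100-200 μg of T3 per 24 h. Some were treated for up to 28 days, without significant adverse events.

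**Population.** Section 4.2 has no renal or hepatic exclusion. Section 12 lists renal failure and hepatic failure among the expected serious adverse events.

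**Monitoring of levels.** Section 5.4 schedules samples at baseline, 24, 48 and 72 h and then every 3 days, but says: "All samples for thyroid hormone measurements will be collected and analyzed at the end". The stated reason is to protect the blind. Section 9 gives one exception. After an event possibly linked to T3 in a patient with severe renal failure, that patient can be unblinded urgently and T3 measured. Section 8 gives the Data Monitoring Committee access to unblinded data, and section 14 schedules interim analyses after 15 and 30 patients.

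**The concern.** The investigational drug is T3 itself. Reduced T4-to-T3 conversion cuts the patient's own production but has no bearing on how fast infused T3 is cleared, so it cannot serve as the safeguard for an infused dose. The protocol has also used the same fact already: inhibited conversion in these patients is its reason for continuing T3 after 48 h.

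The citations do not help. The renal statement carries reference 37, which section 18 lists as a study of immune responses to HSV-1 antigens. The hepatic statement carries reference 38, listed as a study of herpes zoster risk. The hepatic text also names a fulminant hepatitis paper by title, so the numbering may have slipped. As printed, neither number supports the sentence it is attached to.

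At stake is the exposure of patients in renal or hepatic failure, for whom the cited safety data are thinnest. The interim analyses are meant to detect harm and to let the committee judge the design assumptions, yet no section gives the committee T3 levels at those looks.

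**Working it through.** **1. Reproduce the plan's dose figures (Dosage schedules, 77 kg example).**
- First 48 h: 0.113 × 77 × 24 = 208.8 μg per 24 h. By pump: 210/250 × 10.4 × 24 = 209.7 μg. The protocol states 210 μg.
- From day 3: 0.057 × 77 × 24 = 105.3 μg per 24 h. The protocol states 105 μg.

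Both reproduce. The schedule varies with weight only.

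**2. Effect of renal function on infused T3.** At steady state, level = infusion rate / clearance. Let f be the renal share of clearance (0.70-0.80, from the protocol) and g = GFR/100. Assumptions not in the documents: linear kinetics, renal clearance proportional to GFR, a normal GFR of 100, and the 70-80% (stated for thyroid hormones in general) read as the GFR-dependent share for T3.

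Multiplier = 1 / ((1 − f) + f × g)

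| GFR | f = 0.70 | f = 0.80 |
|---|---|---|
| 30 | 1/(0.30 + 0.21) = 1.96 | 1/(0.20 + 0.24) = 2.27 |
| 0 | 1/0.30 = 3.33 | 1/0.20 = 5.00 |

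**3. Half-rate maintenance against the full rate with normal kidneys.** Multiply by 0.5.
- GFR 30: 1.96 × 0.5 = 0.98 to 2.27 × 0.5 = 1.14.
- No renal clearance: 3.33 × 0.5 = 1.67 to 5.00 × 0.5 = 2.5.

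**4. How much can lost conversion offset?** Assume the patient's own T3 input is 10-40 μg/day (not in the documents) and falls to zero, which is the most favourable case for the protocol's argument. With maintenance at 105 μg/day and own input E, total T3 relative to normal = 105 × multiplier / (105 + E).
- GFR 30: 105 × 1.96/145 = 1.42 to 105 × 2.27/115 = 2.07.
- No renal clearance: 105 × 3.33/145 = 2.41 to 105 × 5.00/115 = 4.57.

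Total T3 stays above normal throughout, so the offset is partial.

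**5. Coverage of the safety data.**

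| | GFR | Longest infusion |
|---|---|---|
| ThyRepair | above 60 ml/min | 48 h |
| 11-patient septic shock study | not given | up to 28 days, some patients |
| This trial | no limit | up to 30 days |

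**The case against.** Much can be said for the plan. It does not ignore the problem: it admits the possible rise and says blunted, not abolished. Blood T3 is the sum of endogenous and infused hormone, so lower production does reduce the total. Deferring assays is a deliberate choice with a stated reason. ECG, heart rate, blood pressure, urine volume, laboratory tests and adverse events are recorded every 24 h in the ICU, and the committee can stop the trial.

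Four stronger readings that a reader might infer do not stand:
- **That over-exposure stays invisible until the trial ends.** The unblinding route in section 9 allows an earlier T3 measurement, and the committee sees unblinded data.
- **That events could never be linked to exposure.** Serial samples are kept, so the link can be made at the final analysis.
- **That no data support a long infusion.** The septic shock study used 100-200 μg per 24 h, a range that includes the 105 μg maintenance dose at 77 kg. Comparing cumulative dose with ThyRepair alone would therefore be selective.
- **That half-rate maintenance at GFR 30 always reaches the full-rate level.** At a 70% renal share it gives 0.98.

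Two parts of the concern survive. The conversion argument is still not a safeguard for infused T3, and the septic shock study has 11 patients and no renal data. The reactive route needs someone to suspect T3. Arrhythmia, hypotension, myocardial infarction and heart failure appear in section 12 both as T3 side effects and as expected events of the disease, so that suspicion may not arise. Each use also costs that patient's blind.

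**Conclusion.** The point holds as a fault in the safety rationale combined with a gap in monitoring. The conversion argument cannot carry the weight placed on it for renal or hepatic failure, and the ThyRepair and septic shock data do not cover long infusion in renal failure. Over-exposure is not monitored prospectively. Before the end, levels can be seen only by unblinding a patient after a suspected T3-related event.

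The figures in the working are conditional illustrations of size, not estimates. They depend on the kinetic assumptions listed there, and the documents show no actual over-exposure. The monitoring conclusion reads the end in section 5.4 as the end of the trial, which is the natural reading but is not spelled out. Nothing here says that the dose is wrong.

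**What to change.** **Section 5.4.** Keep sites and investigators blinded, but assay the samples already collected in batches at the 15- and 30-patient interim analyses. Give T3, T4 and TSH by arm, time on drug and concurrent creatinine, next to adverse events, only to monitoring committee members who already have unblinded access. Such results reveal the arm, so the route must be closed to everyone else. Section 14 places the sponsor's representative on the committee, so the amendment should name by role who receives them.

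**Section 9.** Remove reduced conversion as a safeguard for infused T3 in renal and hepatic failure. State that ThyRepair does not cover GFR of 60 ml/min or below, or infusion beyond 48 h, and that the septic shock study has 11 patients without renal data. Correct references 37 and 38.

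**Reconcile** section 5.4, the maintenance rationale, the renal and hepatic text and the weight-only dosage table. No dose or clinical rule is proposed here.

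**Cost.** The samples and assays are the same, run in three batches instead of one, with some between-batch variation and a short amendment. The interims follow completed follow-up, so the gain is for later patients, not for those already analysed.

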## Dosage schedules

Dosage schedules are summarized in the following table.

| **Patient weight** | **Bolus administration over 2-3 min** | **Continuous infusion** | **Pump rate**  **(first 48h)** | **Pump rate**  **(from day 3 till end)** |
| --- | --- | --- | --- | --- |
| 66Kg | 5.5 ml (55μg) | 18ml (180μg) in 232 ml NaCl 0.9% | 10.4 ml/h | 5.2 ml/h |
| 70Kg | 5.5 ml (55μg) | 19ml (190μg) in 231 ml NaCl 0.9% | 10.4 ml/h | 5.2 ml/h |
| 74Kg | 6 ml (60μg) | 20ml (200μg) in 230ml NaCl 0.9% | 10.4 ml/h | 5.2 ml/h |
| 77Kg | 6 ml (60μg) | 21ml (210μg) in 229ml NaCl 0.9% | 10.4 ml/h | 5.2 ml/h |
| 81Kg | 6.5 ml (65μg) | 22ml i(220μg) n 228ml NaCl 0.9% | 10.4 ml/h | 5.2 ml/h |
| 85Kg | 7.0ml (70μg) | 23ml (230μg) in 227ml NaCl 0.9% | 10.4 ml/h | 5.2 ml/h |
| 89Kg | 7.0ml (70μg) | 24ml (240μg) in 226ml NaCl 0.9% | 10.4 ml/h | 5.2 ml/h |
| 92Kg | 7.5ml (75μg) | 25ml (250μg) in 225ml NaCl 0.9% | 10.4 ml/h | 5.2 ml/h |
| >95Kg | 7.5ml (75μg) | 26ml (260μg) in 224ml NaCl 0.9% | 10.4 ml/h | 5.2 ml/h |

For example, for a patient of 77Kg of weight, a dose of 6ml (60 μg) will be administered as a bolus intravenously over 2-3 min within 60 min of respiratory support initiation. Then, the patient for the next 24 hours will receive 21ml of the product (total of 210 μg of T3) that will be diluted in NaCl 0.9% and administered with a pump at a steady flow rate of 10.4 ml/h for a total duration of 48 hours. From day 3 till successful weaning or end of follow-up, the patient will receive 50% of this dose, 10.5 ml of the product (total of 105μg of T3)that will be diluted in NaCl 0.9% and administered with a pump at a steady flow rate of 5.2 ml/h.

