**4.1 MAIN INCLUSION CRITERIA**

- *Patients diagnosed with pulmonary infection and/or ARDS (COVID-19) due to SARS-Cov2viral infection, admitted in ICU and require mechanical ventilation or ECMO*
- *Male and female with Age>18 years old*
- Consent to use an effective contraceptive method beginning from patient enrolment and during participation in the trial, if potential fertile women are enrolled
- *Signed informed consent*

Potential fertile women enrolled in the study will undergo a pregnancy test that will exclude any possibility of present pregnancy. As potential fertile woman is considered every woman who has a menstrual cycle and has not been subjected in surgical sterilization or is not in a post-menopausal condition. In the case of pregnancy, the patient will immediately and automatically be excluded from enrolment and all necessary assistance will be guaranteed for the mother and the child and the pregnancy will be followed until the delivery.

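### The dosing table gives one fixed dose to everyone above 95 kg, which departs from the uncapped per-kg regimen in the text; weights below 66 kg and the maintenance bag volume are also left open

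*Protocol*

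**What the plan says.** The *Dosage and Safety* part of section 9 defines treatment by body weight: "the dose administered will be 0.8μg/kg i.v. bolus", then 0.113 μg/kg/h for 48 hours, after which "a maintenance dose will be administered corresponding to 50% of the therapeutic dose", given as 0.057 μg/kg/h. It mentions no upper or lower weight and no maximum dose. Section 4.1 admits "Male and female with Age>18 years old", and neither section 4.1 nor section 4.2 restricts weight.

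The *Dosage schedules* part of section 9 turns this into a table with rows from 66 kg to 92 kg and a last, open-ended row for more than 95 kg. That last row is a 75 μg bolus and 260 μg in 26 + 224 = 250 ml. Every row's bag totals 250 ml and every row has the same two pump rates; the 77 kg row, for example, ends "in 229ml NaCl 0.9% | 10.4 ml/h | 5.2 ml/h". The table therefore reaches maintenance by halving the pump rate on an unchanged bag.

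The worked example for 77 kg starts with 21 ml (210 μg) for 24 hours at 10.4 ml/h. From day 3, "the patient will receive 50% of this dose, 10.5 ml of the product" (105 μg), diluted in saline and run at 5.2 ml/h. The final volume is not given.

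**The concern.** A per-kg regimen and a fixed dose for all patients above 95 kg cannot both be followed. A site using the table gives a heavy patient less per kg than the text states, and nothing says that a cap is intended.

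The table also offers nothing to an eligible patient below 66 kg. The maintenance example reduces both the drug volume and the pump rate, so the dose delivered depends on a volume that the protocol does not state. Maintenance can fill up to 30 − 2 = 28 of the 30 treatment days.

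The staff giving the infusion are blinded (section 8). Thyroid hormone samples, which the protocol relies on to document compliance, are analysed only at the end (section 5.4), so routine monitoring would not show a preparation error during treatment. The active arm has 30 patients, and up to three sites may each read the instructions in their own way.

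**Working it through.** **Inputs.** The per-kg doses come from *Dosage and Safety*. The bag contents, volumes and pump rates come from the table and example in *Dosage schedules*.

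**Formulas.** Bolus per kg = μg ÷ kg. Infusion per kg per hour = (μg in bag ÷ total ml) × ml/h ÷ kg.

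**1. Reproducing the stated regimen (77 kg row).**
- Bolus: 60 ÷ 77 = 0.779 μg/kg (stated 0.8; −2.6%).
- First 48 h: 210 ÷ 250 × 10.4 ÷ 77 = 0.1135 μg/kg/h (stated 0.113).
- Maintenance by the table: 210 ÷ 250 × 5.2 ÷ 77 = 0.0567 μg/kg/h (stated 0.057).

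Across all rows, with the last row taken at 95 kg, the bolus runs from 0.779 to 0.833 μg/kg (−2.6% to +4.2%), the infusion from 0.1122 to 0.1139 μg/kg/h (within 1%) and maintenance from 0.0561 to 0.0569 μg/kg/h. In this range the table implements the text.

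**2. Above 95 kg (75 μg; 260 μg in 250 ml at 10.4 ml/h).** The infusion is 260 ÷ 250 × 10.4 = 10.816 μg/h at any weight.

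| Weight | Bolus, μg/kg | vs 0.8 | Infusion, μg/kg/h | vs 0.113 |
|---|---|---|---|---|
| 100 kg | 75/100 = 0.750 | −6% | 10.816/100 = 0.108 | −4% |
| 120 kg | 75/120 = 0.625 | −22% | 10.816/120 = 0.090 | −20% |
| 150 kg | 75/150 = 0.500 | −38% | 10.816/150 = 0.072 | −36% |

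**3. Below 66 kg.** No row applies. Assume that a site uses the 66 kg row (55 μg; 180 μg in 250 ml). Then:
- 60 kg: 55 ÷ 60 = 0.917 μg/kg (+15%) and 180 ÷ 250 × 10.4 ÷ 60 = 0.125 μg/kg/h (+10%).
- 50 kg: 55 ÷ 50 = 1.10 μg/kg (+38%) and 180 ÷ 250 × 10.4 ÷ 50 = 0.150 μg/kg/h (+33%).

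If the site computes from the per-kg figures instead, there is no departure.

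**4. Maintenance example, 77 kg, 105 μg at 5.2 ml/h.**
- Read as a 24-hour quantity: 5.2 × 24 = 124.8 ml, about 125 ml. Then 105 ÷ 125 × 5.2 ÷ 77 = 0.0567 μg/kg/h, which matches 0.057.
- Made up to the table's 250 ml: 105 ÷ 250 × 5.2 ÷ 77 = 0.0284 μg/kg/h, half of 0.057 (about 52 μg per 24 h instead of 105).

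**5. The 24 h and 48 h wording.** 250 ÷ 10.4 = 24.0 h, so one bag lasts one day. Running at 10.4 ml/h for 48 hours needs a second bag.

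**The case against.** The best defence is that the text governs and the table only summarises it. A site can compute any dose from the per-kg figures, and over most of the table's range the two agree closely. This answers much of the point about low weights: the +38% and +33% at 50 kg depend on a nearest-row rule that the protocol does not contain. A reader might infer that light patients will be overdosed; the documents show only that no row covers them.

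A reader might also infer that the worked example delivers half the stated maintenance dose. The documents do not support that either. The example begins with a 24-hour quantity, so 10.5 ml is most naturally the amount for 24 hours. At 5.2 ml/h this needs about 125 ml, keeps the table's concentration of 0.84 μg/ml (210 ÷ 250 = 105 ÷ 125) and gives 0.057 μg/kg/h. On that reading, the two reductions are one halving described twice. What stands is that the volume is not written down and the only bag volume on the page is 250 ml.

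The 24 h and 48 h wording is not a conflict of dose. Rate and daily amount agree, and only the change of bag is left unsaid.

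The defence does not reach the row above 95 kg. That row is an explicit instruction, it is not a rounding of the text, and no cap is stated that would explain it. The departure is small near 95 kg, and the documents give no weight distribution, so the number of patients affected is unknown.

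**Conclusion.** The firm finding is the contradiction above 95 kg: the text scales the dose with weight without limit, while the table stops scaling. The shortfall against the text grows from about 6% (bolus) and 4% (infusion) at 100 kg to 38% and 36% at 150 kg. It rests on no assumption beyond a site following the table.

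Two preparation ambiguities are secondary. Patients below 66 kg have no row, and any misdosing there depends on what the site does. The maintenance example has no final volume and allows either 0.057 or 0.028 μg/kg/h, with the 24-hour framing favouring the former.

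It would go too far to say that sites will generally give different exposures, or that the primary comparison is compromised. Table and text agree from 66 to 95 kg, and no effect on the primary endpoint or on power has been shown. The point matters for the safe and uniform preparation of a blinded infusion.

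**What to change.** The sponsor should reconcile *Dosage and Safety* with *Dosage schedules* in section 9:

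- State whether the fixed dose above 95 kg is intended, and make text and table agree.
- Either cover the whole eligible weight range in the table, or state the weight limits and how patients outside the rows are handled.
- Give one maintenance preparation (drug volume, total volume, pump rate and hours per bag) that is consistent with the stated maintenance dose. State the bag change in the first 48 hours in the same place.

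Which regimen applies, and whether there is a cap, is a clinical decision for the sponsor; no dose is proposed here. The cost is a corrected table and example in an amendment and in the pharmacy instructions. Sample size and analysis are unaffected.
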